### Study design

A randomized controlled trial will be conducted with adolescents who will be randomly assigned by gender to a control or experimental group.

The experimental group will perform cognitive training through the GGED-AD module; while the control group will use another module of the app, named GGNEUTRAL (Fig. 2). The study will consist of a pre-assessment (T1) and then participants will have to use the corresponding application for a period of 14 consecutive days, for approximately 5 min a day. After completing all levels, a subsequent evaluation (T2) will be carried out, as well as a follow-up evaluation one month after having completed the app module (T3), in order to evaluate whether the possible changes are maintained over time. Figure 2 and Table 1 show the organizational chart of the study.

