### Study procedure

First, an interview will be held with the school leadership team and/or heads of the guidance department of different schools in the Valencian Community, to explain the research objectives, describe the evaluation instruments, request permission to apply them, and encourage their collaboration. The schools interested in participating will distribute an information sheet specifying the objectives and characteristics of the study among the students and their families. Parents of students interested in participating in the study will have to sign the informed consent form authorizing their children to participate in the research. Students themselves must also sign it. The participants that enroll in the study will be randomly assigned by gender to the experimental and control groups using the Random.org program. On the first day of the intervention at the school center, there will be an informative session for the students to explain guidelines for their participation in the study. This will include the importance of being quiet and the option to stop participating at any time. Additionally, there will be assistance provided for the administration of the first evaluation (T1). T1 evaluation will include the evaluation instruments, and sociodemographic data, which will include information on gender, age, school, grade and academic group, height, weight. Once T1 is completed, participants will download the corresponding app to start completing the daily levels. The experimental group will use the GGED-AD app, and the control group will use the GGNEUTRAL app, named GGA and GGN respectively to avoid giving excessive information to participants. Specifically, both apps are divided into 14 blocks, and the participants will do one block each day. Each block has 4–5 levels, which is equivalent to approximately 4–5 min. During this time, members of the research group will be present in the classroom on school days, to solve possible doubts and to control the use of the application. During non-school days participants will have to complete the app at home. After completing the app, all participants will carry out the second evaluation (T2). This evaluation will be composed of the same set of questionnaires completed at T1. Once T2 is completed, the adolescents will receive instructions to not use the application until we contact them again to conduct the follow-up after one month (T3) to evaluate if the possible changes achieved are maintained over time. If someone has difficulties or feels uncomfortable during the completion of the evaluation of the module, they will be free to speak to members of the research group who, in case of it being necessary, will be referred to the school counsellor, and in addition will show them different services where they could find help for possible mental health problems.

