### Statistical analysis

Statistical analyses will be performed using the free software R. To avoid overly optimistic estimates of the efficacy of the experiment, an intention to treat (ITT) approach will be used, using the method of the multivariate imputation by chained equations algorithm (MICE) [64].

Descriptive statistics will be used to report means, standard deviations and frequencies. In addition, tests will be performed to evaluate differences between the different variables considered in the study. To predict the different response variables under study, mixed models for repeated measures (MMRM) will be used, in which the outcomes measures are dependant variables, and the independent variables are group of the study (experimental or control), gender (male/female/other) and time (T1, T2, and T3). In addition, the baseline scores for each of the factors evaluated will be used as covariates to control that the T1 scores do not affect the results of the efficacy of the app.

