### Challenges

Some challenges that may be encountered when carrying out the study are: (1) making a schedule that interrupts the lessons as little as possible; (2) that the participants use the application properly, in silence and focused while reading the sentences; (3) that participants complete the app during weekends. In order to overcome these challenges, the researchers will meet with the team of teachers to agree on a procedure that will cause as little disruption as possible to their work. In addition, the researchers will be there every day to accompany the adolescents as they complete the app, to remind them of the importance of completing the app seriously, to see that they do not answer randomly and to encourage them to complete the app over the weekend. It is possible that the number of dropouts will be higher than expected. Thus, the goal is to motivate participants as much as possible to minimize the dropout rate.

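### T2 and T3 are timed by finishing the app, so a student who does not finish has no defined assessment date, which may work against the intention-to-treat aim

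*Protocol article*

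**What the plan says.** Two sections of the protocol article say when outcomes are measured.

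- **Study design.** Participants are to "use the corresponding application for a period of 14 consecutive days". Then: "After completing all levels, a subsequent evaluation (T2) will be carried out", followed by "a follow-up evaluation one month after having completed the app module (T3").
- **Study procedure.** "both apps are divided into 14 blocks, and the participants will do one block each day". Then: "After completing the app, all participants will carry out the second evaluation (T2"). T3 follows from T2: "Once T2 is completed, the adolescents will receive instructions to not use the application until we contact them again", which is to happen after one month.

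The Statistical analysis section states its purpose: "To avoid overly optimistic estimates of the efficacy of the experiment, an intention to treat (ITT) approach will be used", with missing values handled by multivariate imputation by chained equations (MICE). The outcome model contains group, gender, time and baseline score. The imputation model is not described.

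The article expects that some students will not finish. Students may stop at any time and work at home on non-school days (Study procedure). The Challenges section lists "that participants complete the app during weekends" among the difficulties and allows that dropout may exceed expectation.

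**The concern.** An intention-to-treat analysis needs outcomes to be sought from everyone randomised, whatever their adherence. Here the event that triggers the outcome assessment is adherence itself. A student who stops at block 9 never reaches the trigger. A student who misses several home days reaches it late, and T3 moves with it.

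Imputation can stand in for values that were sought and not obtained, but it rests on assumptions. If the missing values belong mainly to students who stopped using the app, and are predicted from students in the same arm who finished, the result is close to the effect had everyone finished. That differs from the effect of being assigned to the app, and it is usually the more favourable of the two. An analysis plan can refine the imputation model, but it cannot recover T2 and T3 data that were never collected.

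**Working it through.** The article gives no figure on this point to reproduce. The check has two parts: what the timing rules imply, and how large the effect could be under stated assumptions.

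**1. Timing rules**

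| Student | T2 | T3 |
|---|---|---|
| Finishes on day 14 | after day 14 | one month after completion |
| Finishes *k* days late | *k* days later | *k* days later |
| Never finishes | no date given | no date given |

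A calendar anchor exists (14 consecutive days), but neither assessment is dated from it. Any 14 consecutive days contain four weekend days, so at one block a day at least 4/14 = 29% of the blocks fall on days without a researcher in the classroom. Falling behind is therefore foreseeable.

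**2. Possible size**

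All of these inputs are assumptions, because the article gives none of them:
- *d*: effect of the app in students who finish.
- *p*: share of the experimental arm that does not finish.
- *t*: fraction of *d* that non-completers would show if assessed.
- Every non-completer lacks T2, is imputed from completers in the same arm, and does not otherwise differ in prognosis.

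Effect of assignment: *d* × [(1 − *p*) + *p* × *t*].

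Effect after imputation from completers: *d* × [(1 − *p*) + *p*] = *d*.

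Relative overstatement: 1 / [(1 − *p*) + *p* × *t*] − 1.

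| *p* | *t* = 0 | *t* = 0.5 | *t* = 1 |
|---|---|---|---|
| 10% | 1/0.90 − 1 = 11% | 1/0.95 − 1 = 5% | 0% |
| 20% | 1/0.80 − 1 = 25% | 1/0.90 − 1 = 11% | 0% |
| 30% | 1/0.70 − 1 = 43% | 1/0.85 − 1 = 18% | 0% |

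**Simulation check.** This used 34 students per arm (the planned 68 split equally), a baseline correlation of 0.7 and *d* = −0.5 SD, all assumed, with multiple imputation from baseline score and arm. With *t* = 0 and equal non-completion in both arms, the mean imputed estimates were −0.51, −0.50 and −0.49 at *p* = 10%, 20% and 30%. The true effects of assignment were −0.45, −0.40 and −0.35. With *t* = 1 the imputed and true values agreed.

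**Direction.** Suppose non-completers also score 0.5 SD worse for reasons unrelated to the app, with *t* = 0.
- 10% non-completion in the experimental arm and 30% in the control arm: true effect −0.5 × 0.90 + 0.5 × (0.10 − 0.30) = −0.55. Imputation gave −0.50, an understatement.
- Rates swapped (30% and 10%): true effect −0.5 × 0.70 + 0.5 × (0.30 − 0.10) = −0.25. Imputation again gave −0.50, a larger overstatement.

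The sign and size therefore depend on who fails to finish, as well as how many.

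**The case against.** The strongest reply is that the wording describes the ordinary sequence and does not make completion a condition for assessment. Study procedure says that all participants do T2. The app runs to a daily plan over a fixed period, with researchers in class on school days. The Results section plans one month of data collection and a follow-up one month later, and the note to Table 1 defines T3 simply as one month later. The bodies of Fig. 2 and Table 1 are not shown. This reading is possible. It does not close the gap, because the reference to all participants is itself tied to having completed the app, and no sentence dates T2 for a student who has not.

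A reader might go further than the text allows in four ways:
- **That non-completers have no outcome.** No sentence excludes them from T2 or T3.
- **That the analysis is not intention to treat, or imputes non-completers as completers.** The article drops no randomised student and does not give the imputation model. That model, including any use of app-usage data, may be set out in an analysis plan that is not at hand.
- **That efficacy will be overstated.** The bias is zero if non-completers benefit equally, and it can reverse.
- **That the T1–T2 or T1–T3 intervals will differ between arms.** Both apps have the same block structure, supervision and trigger, and nothing suggests different completion speeds.

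It is also fair to say that students who withdraw altogether would be missing under fixed dates too. The percentages therefore overstate what a change of timing alone would recover.

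**Conclusion.** The point holds as a gap in the assessment schedule. T2 and T3 are both anchored to finishing the app, so a randomised student who does not finish has no defined date and a slow one is assessed late. Followed literally, this makes non-adherence a cause of missing outcomes and puts the stated purpose of the intention-to-treat approach at risk.

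The bias is conditional. It needs non-completers to go unassessed, to benefit less, and to be imputed from completers in their arm. On those assumptions the illustrative range is 5% to 43% for 10% to 30% non-completion, with *t* between 0 and 0.5. These figures are an upper bound on the contribution of the timing rule, given non-completion unrelated to prognosis. They are not a forecast, and no stated figure in the article is wrong on this point.

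**What to change.** Amend the two timing statements (Study design and Study procedure) so that T2 takes place on a fixed day after the 14-day window, for example the next school day, and T3 one month after that date. State that this applies to every randomised student whether or not the app was finished, and that all these data are analysed by arm. Study procedure also tells students not to use the app after T2; the investigators should say how that instruction applies to a student who is unfinished on the fixed day.

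Optionally, for outcomes still missing, add a sensitivity analysis that imputes from the control arm, unless the analysis plan already has one.

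The cost is about two sentences and, if the option is taken, one further analysis run. Researchers are already in the classroom. The downside is small: the estimated effect may be slightly smaller. The change has to be made before the first T2, because assessments not held cannot be recovered later.

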**Fig. 2 Fig2:**
[figure not shown]
Organizational Chart of the Study. Note. 14 days using GGED-AD: use of the GG Eating Disorders – Adolescents module during 14 days; 14 days of GGNEUTRAL: use of the GG Neutral module during 14 days

**Table 1 Tab1:**
[figure not shown]
Schedule of enrolment, allocation, intervention, and assessments within according to SPIRIT

Note. T(-1)= enrolment; T0 = allocation; T1= baseline assessment; T2 = post assessment; T3= follow-up assessment 1 month later; EDBQ = Eating Disorder Beliefs Questionnaire; EDE-Q = Eating Disorder Examination Questionnaire; BAS-2 = Body Appreciation Scale-2; PH-4 = The Patient Health Questionnaire; SISE = Single-Item Self-Esteem Scale; EDI-3 = Eating Disorder Inventory

### Intervention

The study groups will complete two different modules of the GGtude platform. The experimental group will complete the GGED module adapted to adolescents (GGED-AD) and the control group will complete the GGneutral module. Both modules are described below.

#### GG eating disorders – Adolescents (GGED-AD)

The GGED-AD is the adaptation of the GGED for adolescents, which is used to work on dysfunctional beliefs associated with eating disorders [51]. The adaptation consisted of three phases. First, a group of researchers with expertise in eating disorders selected statements that may be difficult for teenagers to understand. Of the 708 statements that make up the application, a total of 131 statements were selected. Subsequently, an ad hoc questionnaire was created and administered to adolescents (*n* = 5, *M*_*age*_ = 12, *SD* = 0, 60% female). In this questionnaire, participants indicated their level of understanding of sentences on a visual scale with three response options (green: “I understand it perfectly”; yellow: “I don't quite understand it”; red: “I don’t understand it”). Subsequently, the teenagers had to propose an alternative for the sentences marked as “yellow”. Of the 131 statements selected in the first phase by the group of experts, 88 presented comprehension problems for the participants in this second phase. Finally, in the third phase, the appropriateness of the alternative statements proposed by the participants was evaluated by four psychology PhD researchers (Corberán et al., 2023).

Similar to the GGED module, the GGED-AD is made up of the topics that are normally worked on in CBT in relation to eating disorders [10]. The final version of the GGED-AD includes the following topics: perfect physical appearance, fear of being judged, fear of body fat, body as an object, control of body weight, need for control, fear of complacency, self-esteem, fear of food-related thoughts, physical appearance in the media, fear of shame, negative internal image, and fear of abandonment. As in the adult's version, the sentences from these themes have to be "accepted" or "rejected" based on their adaptiveness. This module will be used by participants in the experimental group.

#### GG neutral module (GGNEUTRAL)

This a module belonging to the GGtude digital platform GGED designed exclusively for research purposes. The operation is similar, sentences appear in the center of the screen, but in this case, the person must accept those sentences that are true (e. g., "Madrid is the capital of Spain"), by dragging them to the top of the screen; and reject those that are false (e. g., "Tokyo is the capital of Spain"), by dragging them to the bottom of the screen. All the statements that compose it are totally independent of the target of the study, thus, there is no sentences related to weight or physical appearance. To use this module in the present study and facilitate its understanding, some sentences were modified to the Spanish context of the teenagers. For example, “Arizona is a state in the USA” was replaced by “Valencia is a city in Spain”. This module will be used by participants in the control group.

### Outcome measures

#### Primary outcomes

*Eating Disorder Beliefs Questionnaire (EDBQ;* Cooper et al., 1997 [52]). It is composed of 32 items that examine core beliefs about weight, physical appearance and eating that are associated with eating disorders. Items are rated on an analog scale from 0 to 100, being 0 “I do not usually believe this at all” and 100 “I am usually completely convinced that this is true”. It contains four subscales: negative self-beliefs, weight and shape as a means of acceptance by others, weight and shape as a means of self-acceptance, and control over eating. In its original version, it presents Cronbach's α values between 0.94, 0.95, 0.90 and 0.89 respectively. Given that there is no validated Spanish version of this questionnaire, the present study will use the translation-retranslation method [53]. First, a minimum of two native Spanish-speaking members of the research team will perform the forward translation of the original questionnaire into Spanish independently. Subsequently, a meeting will be held with the individuals who carried out the forward translation and the rest of the research team. During this meeting, a consensus on the translation of the questionnaire will be reached. This Spanish version will be sent to a native English speaker who, totally blind to the original version, will back-translate it into English. Again, the research team, composed by mental health professionals as well as psychometricians, will check that the back-translation and the original questionnaire match. In the present study, the psychometric properties of the instrument translated into Spanish will be calculated to check its reliability and validity.

#### Secondary outcomes

*Eating Disorder Examination Questionnaire* (*EDE-Q*; Fairburn & Cooper, 1993 [54]; Spanish version: Peláez-Fernández et al., 2012 [55]). It is a 36-item self-report questionnaire that assesses the range, frequency and severity of behaviors associated with a diagnosis of an eating disorder. It comprises four subscales (restriction, food concern, weight concern and figure concern) which are composed of attitudinal and behavioral items. For the present study, we will only use 22 attitudinal items. Items are scored on a 7-point Likert-type scale, ranging from 0 (“No day/ No time/ Not at all”) to 6 (“Every day/ Always/ Completely”). Its original version and its validation in Spanish present an adequate internal consistency (Cronbach's α is 0.86, 0.75, 0.93 and 0.74 for the four scales).

*Body Appreciation Scale-2 (BAS-2;* Tylka & Wood-Barcalow, 2015 [56]; Spanish version: Swami et al., 2017 [57]). It is a single-factor questionnaire that evaluates body satisfaction with 10 items on a 5-point Likert scale (from 1 = “Never” to 5 = “Always”). Both its original and Spanish versions present high internal consistency with Cronbach's α above 0.90.

*The Patient Health Questionnaire (PHQ-4;* Kroenke et al., 2009 [58]; Spanish version: Lenz & Li, 2022 [59]). This is a 4-item measure of two factors: depression and anxiety. It assesses the symptoms experienced by participants during the 2-week period before taking the survey (two items are used for the main symptoms of anxiety and two for depression). The response format is a 4-point Likert-type scale (from 0 = “Never” to 3 = “Almost every day”), and its validation presents adequate psychometric qualities, with an internal consistency (Cronbach's α) of 0.86 (depression) and 0.91 (anxiety).

The *Single-Item Self-Esteem Scale (SISE*; Robins et al., 2001 [60]) is a self-report measure in which the person has to indicate how the statement “I have high self-esteem” describes him/her on a 9-point scale (from 1 = "Not very true for me" to 9 = "Very true for me"). This scale presents high test–retest reliability and a similar criterion validity coefficient with the Rosenberg Self-Esteem Scale (Rosenberg, 1965 [61]) above 0.80.

*Eating Disorder Inventory (EDI-3;* Garner, 2004 [62]; Spanish version: Elosua et al., 2010 [63]). It evaluates 18 scales with a total of 91 items, with a 6-point Likert scale, ranging from 0 = “Never” to 5 = “Always”. However, in this study only the interpersonal insecurity (7 items) and perfectionism (6 items) factors will be used. These factors present Cronbach's α values of 0.93 and 0.75 respectively at its Spanish validation [63].

### Study procedure

First, an interview will be held with the school leadership team and/or heads of the guidance department of different schools in the Valencian Community, to explain the research objectives, describe the evaluation instruments, request permission to apply them, and encourage their collaboration. The schools interested in participating will distribute an information sheet specifying the objectives and characteristics of the study among the students and their families. Parents of students interested in participating in the study will have to sign the informed consent form authorizing their children to participate in the research. Students themselves must also sign it. The participants that enroll in the study will be randomly assigned by gender to the experimental and control groups using the Random.org program. On the first day of the intervention at the school center, there will be an informative session for the students to explain guidelines for their participation in the study. This will include the importance of being quiet and the option to stop participating at any time. Additionally, there will be assistance provided for the administration of the first evaluation (T1). T1 evaluation will include the evaluation instruments, and sociodemographic data, which will include information on gender, age, school, grade and academic group, height, weight. Once T1 is completed, participants will download the corresponding app to start completing the daily levels. The experimental group will use the GGED-AD app, and the control group will use the GGNEUTRAL app, named GGA and GGN respectively to avoid giving excessive information to participants. Specifically, both apps are divided into 14 blocks, and the participants will do one block each day. Each block has 4–5 levels, which is equivalent to approximately 4–5 min. During this time, members of the research group will be present in the classroom on school days, to solve possible doubts and to control the use of the application. During non-school days participants will have to complete the app at home. After completing the app, all participants will carry out the second evaluation (T2). This evaluation will be composed of the same set of questionnaires completed at T1. Once T2 is completed, the adolescents will receive instructions to not use the application until we contact them again to conduct the follow-up after one month (T3) to evaluate if the possible changes achieved are maintained over time. If someone has difficulties or feels uncomfortable during the completion of the evaluation of the module, they will be free to speak to members of the research group who, in case of it being necessary, will be referred to the school counsellor, and in addition will show them different services where they could find help for possible mental health problems.

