
### Blinding

Adolescents will be randomly assigned to either the intervention or control group and will not be informed about which group they are in. However, in this scenario, maintaining the blinding is not possible because participants are aware of the two different apps. Each individual will be checked to determine whether they use the GGED-AD or GGNEUTRAL app. Research team members need to be aware of which group each participant belongs to in order to guide them correctly through the application process.

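### Allocation (T0) comes before the baseline assessment (T1), so the T1 covariates are measured after randomisation and a student lost in between leaves little to impute from

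*Protocol article*

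**What the plan says.** The order is stated in two places in the Protocol article.

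- **Table 1, note:** "T(-1)= enrolment; T0 = allocation; T1= baseline assessment".
- **Study procedure:** after consent, "The participants that enroll in the study will be randomly assigned by gender to the experimental and control groups using the Random.org program". The informative session on the first day at school follows, then T1. Then: "Once T1 is completed, participants will download the corresponding app to start completing the daily levels".

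On the content of T1, Study procedure states: "T1 evaluation will include the evaluation instruments, and sociodemographic data, which will include information on gender, age, school, grade and academic group, height, weight". On help during T1 it states: "there will be assistance provided for the administration of the first evaluation (T1"; the sentence is passive and names no helper.

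Under Blinding, "Research team members need to be aware of which group each participant belongs to", and the reason given is guidance through the app. The same section says that students are not told their group. It also concedes that blinding cannot be kept up, because there are two different apps.

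Data management and data monitoring says that participants fill in all questionnaires themselves, online. Statistical analysis makes the baseline scores covariates in the mixed models, and specifies intention to treat with multiple imputation by chained equations (MICE).

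**The concern.** A baseline covariate is guaranteed to be independent of arm only if it is measured before allocation. Here the plan fixes the opposite order, and the people who know the allocation may be in the room when students answer. The primary outcome, the EDBQ, is a subjective 0 to 100 rating by adolescents aged 13 to 16, so help or comment during completion could in principle affect it.

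The second issue is the gap between T0 and T1. The first-day session falls in that gap, and it tells students that they may stop at any time. A student who does so, or who is absent that day, has been randomised but has no baseline. The analysis must then either impute the whole record or exclude the student after randomisation, and exclusion would depart from the stated intention to treat.

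**Working it through.** The article gives no figure on this point that could be reproduced, so the check sets its statements side by side.

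**1. Order of steps.** The Table 1 note gives enrolment, allocation, baseline. Study procedure gives consent, randomisation by gender, first-day session, T1, download. The two agree, so the order is a stated design choice and not a slip in one place.

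**2. Who can know the arm at T1.**
- *Staff:* Blinding says that the team must know the arm and does not limit this to the time after T1. The download follows T1 directly, so the allocation has to be available to whoever runs that session.
- *Students:* they are not told their arm and have no app yet. The apps also carry the neutral names GGA and GGN.
- *Helpers at T1:* not identified. They may or may not be team members who know the arm.

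**3. What T1 feeds.** T1 scores are covariates in all the models. Suppose that something linked to arm moved the T1 mean of one arm by δ and left later scores unchanged. With a covariate slope β, the adjusted group difference would move by −β × δ. The documents give neither δ nor β, so no number follows. The facts in step 2 suggest that δ is near zero.

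**4. Loss between T0 and T1.** The planned minimum is 68 (Sample). The article gives no rate of loss for this interval, so the rates below are assumptions:
- one student: 1 / 68 = 1.5%
- 5% lost: 0.05 × 68 = 3.4 students
- 10% lost: 0.10 × 68 = 6.8 students

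For such a student, every questionnaire and the listed sociodemographic data (age, school, grade, academic group, height, weight) would have come from T1. As the article describes it, what remains is the arm and the gender stratum, plus whatever was noted at enrolment. Imputing from these returns roughly the mean of that arm and gender with noise added, and contributes almost no information about the effect of the app.

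**5. Does any step need the allocation before T1?** The only step that uses it is the release of the app, and that already comes after T1. Nothing in the procedure requires the present order.

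**The case against.** The strongest case on the other side is that the safeguards already remove most of the risk. The students are their own raters. At T1 they do not know their arm and have not seen either app, and the loss of blinding that the article concedes arises from the apps. Staff knowledge of the arm is tied to guidance through the app, which starts after T1. The interval between T0 and T1 is not stated and may be short. Students who do not know their arm have no documented reason to drop out differently by arm, so early losses would cost some precision and need not cause bias. All of this stands, and it is why the likely bias is small. It does not change the stated order, the post-allocation status of the covariates, or the near-empty records of early losses.

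A reader might infer more than the article supports:

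- *That the baseline is collected by staff who know the arm.* It is completed online by the student. Help is offered, but the helper is not identified, and nothing says that the arm is used or revealed.
- *That the gender strata must differ from the gender term in the model.* Gender is listed among the T1 data, but the article does not say that it is unknown earlier. It could be recorded at consent or enrolment.
- *That the bias can be given in standard deviations.* Any such figure would multiply one assumed input by another.
- *That an early loss leaves no data at all.* Arm and stratum remain.

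**Conclusion.** The point holds as a modest weakness in sequencing. The article places allocation before baseline in two places, the research team knows the arm, and the T1 scores are covariates, so independence of covariate and arm rests on conduct and is not secured by design. The article does not contradict itself here, and no bias is shown. The likely bias is small, given self-completion, students not being told their arm, and the app arriving only after T1. Its size cannot be calculated from the document. The number of near-empty records depends entirely on an unstated rate of loss: 3.4 of 68 at an assumed 5%, and 6.8 at an assumed 10%. The change is a cheap improvement worth making; the trial does not fail without it.

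**What to change.** Reorder the steps in Study procedure: consent, then T1 including gender, then randomisation of the students who completed T1, stratified on the gender recorded there, then release of the GGA or GGN app. Use that same gender variable in the model. Change the Table 1 schedule and its note so that baseline precedes allocation.

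This makes every covariate pre-allocation by construction, leaves no arm for a T1 helper to know, and gives every randomised student baseline data for the intention-to-treat and MICE analysis.

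It needs no new visit or measurement. The cost is a short allocation step between T1 and the download, on the same or the next day. That adds slightly to classroom logistics, and Challenges already names disruption of lessons as something to keep low. Preparing the allocation sequence for each gender stratum beforehand would keep the step short.
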